### Statistical analysis

The primary analysis will be based on the intention-to-treat principle. As a secondary analysis, we will perform a per-protocol analysis for the primary study outcome. Before the end of the study, a final statistical analysis plan will be completed.

The occurrence of the primary outcome (occurrence of vascular death or a non-fatal stroke) in each of the 2 treatment groups will be expressed as an annual event rate with a 95 % CI. The occurrence of the primary outcomes between the 2 treatment groups will be reported in terms of the hazard ratio with corresponding 95 % CIs, calculated with the Cox proportional hazard model.

The effect of the allocated treatment on the various other outcome events and SAEs will be assessed in the same fashion as the primary study parameter.

We will dichotomise the mRS scores at follow-up into 3 to 6 (poor outcome) and 0 to 2 (good outcome). The effect of the treatment on the mRS will be analysed using risk ratios with a corresponding 95 % CI.

We will adjust the crude hazard ratios and risk ratios for possible baseline incomparability given the size of the study.

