We hypothesise that in patients with AF who survived an anticoagulation-associated ICH, treatment with apixaban may be the best long-term alternative for the prevention of recurrent stroke and systemic thromboembolism. To test this hypothesis, a conclusive phase III, randomised clinical trial comparing the long-term effects of apixaban with those of APDs or no antithrombotic treatment in these patients is required. Before such a trial can commence, a phase II trial is needed to obtain reliable estimates of the rates of vascular death or non-fatal stroke for both strategies in patients with AF and a recent anticoagulation-associated ICH. As a secondary objective, we aim to compare the rates of all-cause death, vascular death, stroke, ischaemic stroke, recurrent ICH, other major haemorrhage, systemic embolism, myocardial infarction, and functional outcome between patients treated with apixaban and those in whom anticoagulation is avoided.

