### Rationale for study treatment

The treating physician will decide on any of the treatment regimens in the comparator group. This design is based on the lack of evidence that any of the treatment options has a more favourable risk-benefit ratio in this population than others [18, 32, 41, 42].

Allowing variable treatment regimens enables us to include patients with or without a medical history of atherosclerotic disease, which could warrant the use of APDs. The choice for these treatment options in the comparator arm enables us to achieve close similarity with current clinical practice and include as many eligible patients as possible to answer the research question.

The physician can include other indications for APDs (e.g., a history of myocardial infarction) in the decision on the treatment in the comparator arm.

Treatment with any of the drugs in the study can commence anywhere between 7 and 90 days after the ICH, at the discretion of the treating physician. There are reports suggesting that VKAs can be resumed after 3 days [43], whereas others recommend resumption of antithrombotic drugs anywhere between 70 and 210 days, if at all [24]. In the absence of evidence on the optimal timing of the resumption of antithrombotic drugs after ICH, we chose this interval as it reflects clinical practice.

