#### Randomisation

Allocation to treatment groups will be based on randomisation through a web-based system. Treatment allocation will be stratified by the choice of treatment in the comparator arm (APD versus no APD) and will use a minimisation algorithm for age (≤75 years versus >75 years) and location of the haemorrhage (lobar versus non-lobar). This treatment allocation ensures that both treatment groups will be comparable with regard to the intended treatment in the comparator arm.

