### Intervention

Patients will be randomised to treatment with apixaban 5 mg or 2.5 mg given orally twice daily, or to treatment with one or two oral APDs (acetylsalicylic acid, carbasalate calcium, clopidogrel, or dipyridamole) or no antithrombotic treatment at all, at the discretion of the treating physician. Details about the allowed treatments in both groups are shown in Table 2. Treatment will start immediately after randomisation and will continue for the duration of the study. If during the course of a patient’s participation in this study the treating physician feels that a particular antithrombotic drug is clearly indicated or contra-indicated, the choice of the antithrombotic drug may be changed.

**Table 2 Tab2:** Possible treatments in both trial arms

Arm 1: apixaban	Arm 2: avoid anticoagulation
Apixaban 5 mg twice daily	No antithrombotic treatment
Apixaban 2.5 mg twice daily^a^	Acetylsalicylic acid 80 mg once daily
	Carbasalate calcium 100 mg once daily
	Clopidogrel 75 mg once daily
	Acetylsalicylic acid 80 mg once daily and dipyridamole 200 mg twice daily
	Carbasalate calcium 100 mg once daily and dipyridamole 200 mg twice daily

^a^Reduced dose: the dose will be reduced if 2 of the 3 following criteria are met: age ≥ 80 years, body weight ≤ 60 kg or serum creatinine ≥133 μmol. If the creatinine clearance is below 30 ml per minute, the dose will also be reduced

Patients in both treatment groups will be treated according to the relevant guidelines for the prevention of stroke or systemic embolism.

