### Sample size estimation

For the population under study, there are no reliable estimates of the occurrence of the primary outcome for each of the tested treatments, and the main aim of this study is, therefore, to obtain such estimates to inform the design of a phase III clinical trial. Inclusion of a total of 50 patients in each of the treatment arms during the first 30 months of the study and 1 final year of follow-up will result in about 100 patient-years of follow-up in each treatment arm. Ten primary outcome events in 100 patient-years of follow-up will yield a 95 % CI of 4.9 to 17.6. This estimate will not only be more reliable because selection bias will not play a major role in this phase II trial, but also be more precise in comparison with the previous retrospective cohort studies.

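### The control-arm rate holds only at this trial's antiplatelet share: stratify the primary Cox model by intended comparator, and show rates by that stratum

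*Protocol article*

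**What the plan says.** All references are to the protocol article.

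- **Aim.** The Background says that "a phase II trial is needed to obtain reliable estimates of the rates of vascular death or non-fatal stroke for both strategies". The two strategies are apixaban and avoiding anticoagulation. Sample size estimation is worded more loosely: it says that there are "no reliable estimates of the occurrence of the primary outcome for each of the tested treatments" and makes obtaining such estimates the main aim, in order to design a phase III trial.
- **Comparator.** Under Rationale for study treatment, "The treating physician will decide on any of the treatment regimens in the comparator group". The Intervention section allows one or two antiplatelet drugs "or no antithrombotic treatment at all, at the discretion of the treating physician". Table 2 lists five APD regimens besides no treatment.
- **Allocation.** The Randomisation section has allocation "stratified by the choice of treatment in the comparator arm (APD versus no APD"). The reason it gives is comparability of the two groups on the intended comparator.
- **Analysis.** The primary outcome "in each of the 2 treatment groups will be expressed as an annual event rate" with a 95% CI, and the arms are compared by a Cox hazard ratio. The section calls the hazard ratios crude and says they will be adjusted for possible baseline incomparability. It names no stratification term. It defers a final statistical analysis plan (SAP), which is not shown.

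**The concern.** The control-arm rate is one of the two main products of this trial. It averages over patients intended for an APD and patients intended for nothing, in proportions that come from physicians' choices.

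The article itself gives reasons why the two parts could differ. The Background reports a modest reduction in ischaemic stroke with APDs, and more major bleeding than with no antithrombotic therapy (incidence rate ratio 1.55). The rationale section lets physicians weigh other indications, such as earlier myocardial infarction, so the patients may differ as well as the treatment. A phase III trial with another APD share could then see another control rate, and the pooled figure alone gives its planners no means of re-weighting.

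The second issue is the model. The stratification factor is balanced by design. Adjustment prompted by baseline imbalance will therefore tend to leave it out, even if it is prognostic, and the analysis would not reflect how patients were allocated.

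**Working it through.** **1. The plan's own figure.** Sample size estimation gives 10 events in 100 patient-years and a 95% CI of 4.9 to 17.6. An exact binomial interval for 10/100 is 4.90 to 17.62, which matches. An exact Poisson interval, the usual choice for a rate, is 4.80 to 18.39. Follow-up per arm with uniform accrual and no deaths or losses is 50 × (2.5/2 + 1) = 112.5 patient-years, consistent with the article's figure of about 100. Both figures describe a whole arm; nothing is sized by stratum.

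**2. Dependence on the mix.** Let *s* be the share of control follow-up in the APD stratum, *a* the rate there and *b* the rate in the other stratum. Then

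pooled rate = *s* × *a* + (1 − *s*) × *b*.

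The article gives none of *s*, *a* and *b*, so all are assumptions (rates per 100 patient-years):

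| *a*, *b* | Values of *s* | Pooled rate |
|---|---|---|
| 8, 14 | 0.2 / 0.5 / 0.8 | 12.8 / 11.0 / 9.2 |
| 5, 15 | 0.3 / 0.5 / 0.7 | 12 / 10 / 8 |
| 8, 12 | 0.3 / 0.5 / 0.7 | 10.8 / 10.0 / 9.2 |
| equal | any | unchanged |

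In the first row, 12.8/9.2 = 1.4, which is the ratio of patient-years needed for a given number of events. Reversing *a* and *b* reverses the direction but not the spread.

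**3. Precision of stratum rates.** The inputs are 100 patient-years and 10 events in the control arm, with an assumed rate of 10 per 100 in both strata. The exact Poisson limits for *d* events in *T* patient-years are χ²(0.025; 2*d*)/(2*T*) and χ²(0.975; 2*d*+2)/(2*T*), multiplied by 100:

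| Events / patient-years | 95% CI per 100 |
|---|---|
| 10 / 100 (pooled) | 4.8 to 18.4 |
| 8 / 80 | 4.3 to 19.7 |
| 7 / 70 | 4.0 to 20.6 |
| 5 / 50 | 3.2 to 23.3 |
| 3 / 30 | 2.1 to 29.2 |
| 2 / 20 | 1.2 to 36.1 |

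**4. Could strata be compared?** With 10 control events and an even split of follow-up, approximate power is Φ(√(10/4) × ln RR − 1.96). For RR = 2 this is Φ(1.096 − 1.96) = 19%. For RR = 3 it is Φ(1.737 − 1.96) = 41%. The stratum figures can describe; they cannot support a comparison.

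**5. The model.** This step is a reading of the text. Allocation uses the intended comparator as a stratum, while the analysis section starts from a crude hazard ratio and adjusts for baseline differences. A factor balanced by stratification will seldom show such a difference. The effect on the hazard ratio depends on how prognostic the stratum is, which the article does not say, so no size is claimed.

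**The case against.** The strongest reply is that the analysis matches the stated target. The Abstract, the Background and Ethical considerations all describe two strategies, and Table 2 names the second arm accordingly. One rate per arm estimates exactly that. This stands, and it is why the pooled rates should remain primary.

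Three stronger readings are tempting, and none is supported.

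- A reader might infer from the wording in Sample size estimation ("no reliable estimates of the occurrence of the primary outcome for each of the tested treatments") that the plan promises a rate for each regimen and then fails to deliver it. The same paragraph sizes two arms of 50 and gives an interval for one whole arm, so this is loose wording and not a contradiction.
- A reader might infer that phase III must pick one comparator, so that in the 8 and 14 example a pooled 11 would be 21% below 14, (14 − 11)/14, or 38% above 8, (11 − 8)/8. The Background envisages a phase III trial with the same mixed comparator, so that error belongs to a design the article does not propose.
- A reader might infer that stratum rates would be the rates of each treatment. The contrast with apixaban within a stratum is randomised, but membership of the stratum is the physician's choice. The Intervention section also lets the drug change during follow-up, and the APD stratum pools five regimens.

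It is also fair to say that the rates used here are assumed, that all of them lie inside the plan's own interval of 4.9 to 17.6, and that the Background cites small studies finding no difference in recurrent intracerebral haemorrhage between acetylsalicylic acid and no antithrombotic drug.

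Finally, the deferred SAP may already contain stratum rates or a stratified model, so nobody can say that they are absent from the trial's plans. That does not dispose of the point, because the article itself states how the primary outcome will be expressed and on what basis the hazard ratio will be adjusted.

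**Conclusion.** The point holds as a limitation for phase III planning and as a mismatch between allocation and the stated model. It is not an error in the estimand. The pooled control rate is valid for avoiding anticoagulation at this trial's APD share and carries over to another share only if the two strata have similar rates. The size is unknown from the article: under the assumed rates above the pooled figure shifts by up to 1.4-fold (8 and 14, share 20% to 80%), and by nothing if the rates are equal. Stratifying the Cox model rests on no assumed rate; it follows from how patients are allocated.

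**What to change.** State the following in the analysis section or the final SAP, before outcome data by arm are seen:

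1. Keep the annual event rate per arm, pooled over strata, as the primary result.
2. Stratify the primary Cox model by the randomisation stratum (intended APD versus no APD), whatever imbalance is observed.
3. Report descriptively the APD share and, by arm within each stratum, the annual event rate with an exact 95% CI. Label these as intended treatment in physician-selected patients.
4. State that no inference will be drawn between strata.

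The cost is one model term and a few table rows. No new data are needed, since the intended comparator must be recorded in order to randomise. The downside is wide stratum intervals that could be over-read, which is why the labelling in items 3 and 4 matters.

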### Study outcomes

The primary outcome is the combination of vascular death or non-fatal stroke (cerebral infarction, ICH, or subarachnoid haemorrhage) during follow-up. Secondary outcomes will be: vascular death, death from any cause, all stroke, ischaemic stroke, ICH, other major extracranial haemorrhage, any intracranial haemorrhage other than ICHd, systemic embolism, myocardial infarction, and functional outcome as assessed with the score on the mRS at 6 and 12 months; annually thereafter; and at the end of the study. Definitions of the clinical events comprising the study outcomes are shown in Table 3.

**Table 3 Tab3:** Event definitions

Ischaemic stroke	Clinical evidence of the sudden onset of a new neurological deficit, or an increase in an existing deficit, persisting for more than 24 hours, without evidence of a intracerebral haemorrhage on a CT or MRI scan or at post-mortem investigation
Intracerebral haemorrhage	Clinical evidence of the sudden onset of a new neurological deficit, or an increase in an existing deficit, persisting for more than 24 hours, with a corresponding intracerebral haemorrhage on a CT or MRI scan or at post-mortem investigation
Unclassified stroke	Clinical evidence of the sudden onset of a new neurological deficit, or an increase in an existing deficit, persisting for more than 24 hours, without imaging or post-mortem investigations performed
Subarachnoid haemorrhage	Subarachnoid haemorrhage (SAH) demonstrated by CT, lumbar puncture, or at post-mortem investigation
Myocardial infarction	Evidence of myocardial necrosis in a clinical setting consistent with acute myocardial ischemia. Under these conditions any one of the following criteria meets the diagnosis for MI [51]:
	● Detection of a rise and/or fall of cardiac biomarker values (preferably cardiac troponin) with at least one value above the 99th percentile upper reference limit and with at least one of the following:
	○ Symptoms of ischemia
	○ New or presumed new significant ST-segment-T wave changes or new left bundle branch block (LBBB)
	○ Development of pathological Q waves in the ECG
	○ Imaging evidence of new loss of viable myocardium or new regional wall motion abnormality
	○ Identification of an intracoronary thrombus by angiography or autopsy
	● Cardiac death with symptoms suggestive of myocardial ischemia and presumed new ischemic ECG changes or new LBBB, but death occurred before cardiac biomarkers

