### Interim analyses

Interim analyses on safety and efficacy will be performed by the Data Safety and Monitoring Board (DSMB) according to the DSMB charter. These analyses are performed after 50, 100, and 150 patient-years of follow-up, and ad hoc as needed.

The interim analyses on both safety and efficacy will be performed on the primary outcome: the occurrence of vascular death or non-fatal stroke. This combined outcome consists of both the main efficacy outcome (ischaemic stroke) events as well as the main outcomes for harm (ICH, fatal vascular event).

The DSMB will compare both treatment arms using a Poisson’s test (Conditional Test) with two-sided testing. For all interim analyses of the primary outcome, a boundary of *P* < 0.01 will be used for any recommendation to terminate the trial.

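### Cox hazard ratios, crude and adjusted, are prescribed for all secondary events and SAEs with no exception for sparse outcomes, so the rarest may yield no finite ratio (minor, cheap to repair)

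*Protocol article*

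**What the plan says.** Protocol article, Statistical analysis: the primary outcome gets an annual event rate with a 95% CI in each arm, and a Cox hazard ratio with a 95% CI between arms. The effect of allocated treatment on the "various other outcome events and SAEs will be assessed in the same fashion as the primary study parameter". The section adds: "We will adjust the crude hazard ratios and risk ratios for possible baseline incomparability given the size of the study". The dichotomised mRS is the exception among the secondary outcomes, because it is analysed by risk ratios. A final analysis plan is announced but not shown.

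The secondary events listed under Study outcomes include some that are likely to be uncommon: "any intracranial haemorrhage other than ICHd, systemic embolism, myocardial infarction".

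Sample size estimation gives the scale of the data. Fifty patients per arm, recruited over 30 months and then observed for one more year, are the design that "will result in about 100 patient-years of follow-up in each treatment arm".

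Under Interim analyses, the monitoring board compares arms on the primary outcome with a Poisson test ("Conditional Test) with two-sided testing"). A rate-based comparison is therefore already in use in this trial, though only for that purpose.

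**The concern.** The article names one between-arm method and applies it to all secondary events whatever their number. A Cox model fitted by maximum partial likelihood needs at least one event in each arm to give a finite hazard ratio. With none in one arm, the likelihood keeps rising as the log hazard ratio moves away from zero. Software then reports a ratio near 0 or a very large one, with an interval running from 0 to infinity. Covariate adjustment adds further ways to fail, because a covariate level without events makes its own coefficient diverge.

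The Background makes comparison of the individual outcomes the secondary objective, and the Discussion says that the data will inform a phase III trial. Where the rule fails, the report would show no usable between-arm interval for that outcome, although an exact method would still give a bound from the same data.

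**Working it through.** **Inputs from the article.** 50 patients per arm, 30 months of accrual, 1 further year, about 100 patient-years per arm (Sample size estimation). Under uniform accrual without death or loss, follow-up is 50 × (15 + 12)/12 = 112.5 patient-years per arm, which agrees with the stated figure.

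**The plan's own figure.** "Ten primary outcome events in 100 patient-years of follow-up will yield" a 95% "CI of 4.9 to 17.6". The exact binomial interval for 10 of 100 is 4.90 to 17.62, so the figure is reproduced. The exact Poisson interval for 10 events in 100 patient-years is 4.80 to 18.39. The difference is small here, but the Poisson form is the one that matches a rate per patient-year.

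**Chance of an empty arm.** With λ expected events per arm and equal rates, P(at least one arm has none) = 1 − (1 − e^−λ)². The rates below are assumptions.

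| Rate per 100 patient-years | e^−λ (100 patient-years) | At least one empty arm (100) | Same, 112.5 patient-years |
|---|---|---|---|
| 0.5 | 0.607 | 0.85 | 0.82 |
| 1 | 0.368 | 0.60 | 0.54 |
| 2 | 0.135 | 0.25 | 0.20 |
| 3 | 0.050 | 0.10 | 0.07 |
| 5 | 0.007 | 0.01 | 0.01 |

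At 100 patient-years, an empty arm is more likely than not only below −ln(1 − √0.5) = 1.23 per 100. At a rate of 1, the 0.60 splits into 0.46 or 0.47 for exactly one empty arm (2 × 0.368 × 0.632 = 0.465) and 0.135 for both (0.368²).

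**Several outcomes together.** Take systemic embolism, myocardial infarction, other intracranial haemorrhage and major extracranial haemorrhage as independent, with assumed rates.
- Rates 0.5, 1, 1, 2: P(at least one outcome has an empty arm) = 1 − 0.155 × 0.400² × 0.748 = 0.98; P(at least two) = 0.82.
- Rates 2, 2, 2, 4: 0.60 and 0.17.
- Rates 3, 3, 3, 3: 0.34 and 0.05.

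**Outcomes for which the Background gives rates** (annual risks read as rates per 100 patient-years).
- Recurrent ICH at 2.3 in both arms: 0.19. At 2.5 versus 10: 0.08. At 8.2 in both arms: below 0.001.
- Ischaemic stroke at the lowest cited value for aspirin or no treatment, 1.3 in both arms: 0.47.
- Some cited ranges for ICH and ischaemic stroke start at 0%, where an empty arm would be certain.

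**What Cox does with 0 versus 3 events.** In an example with 50 patients per arm, the log partial likelihood was −9.847 at log HR 0, −8.368 at −5 and −8.355 at −20. It was still rising and had no maximum. The fit stopped without converging at log HR −23.6 with a standard error of about 95,000.

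**What an exact method does with the same data.** With equal person-time, the upper 95% limit for the share of the 3 events in the empty arm is p = 1 − 0.025^(1/3) = 0.708. The rate ratio limit is 0.708/0.292 = 2.42.

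**Adjusted models.** Assume three binary covariates, each split evenly and unrelated to the outcome, plus treatment. The model has no finite maximum if all events fall in one level of any of the four variables. With n total events, Poisson with mean 2λ, the chance of this is 1 − Σ P(n)(1 − 2^(1−n))⁴, summed over n ≥ 1. This gives 0.83 at 1 per 100 and 0.50 at 2. Simulated trials with three binary covariates gave about 0.84 and 0.49. The corresponding crude figures are 0.60 and 0.25. In some of these cases only a covariate coefficient diverges, and the treatment ratio may still settle.

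**The case against.** The strongest reply is that an article may leave sparse-event handling to the analysis plan, and this one announces such a plan. That settles where the repair may sit. It does not remove the point, because the article does not leave the method open: it names Cox for these events and then adjustment.

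Other parts of the reply stand and limit the claim:
- Assessing the other events in the same way as the primary outcome plausibly includes the per-arm rates. These stay defined with no events: 0 in 100 patient-years has an exact upper limit of 3.69 per 100. Rate estimation is the trial's main aim.
- The article does not specify Wald intervals. With one empty arm, a log-rank test and a one-sided profile-likelihood bound still exist, and a Firth-penalised fit is still a Cox model.
- The monitoring board's test is specified for interim looks at the primary outcome only. It shows that a method is at hand, not that the authors intended it here.
- Adjustment is for possible imbalance, so an adjusted model for each rare outcome may not be intended.

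A reader might infer that several secondary outcomes will probably lack an estimate. The documents do not support this: they give no rates in this population for the rarest outcomes, and the result moves from 0.98 to 0.34 across the assumed sets. Nor do they support saying that every secondary outcome is affected, since the mRS uses risk ratios. Death, all stroke and SAEs, and ICH over most of the cited rates, are unlikely to have an empty arm.

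**Conclusion.** The point holds as a minor one. The stated rule applies crude and adjusted Cox hazard ratios to all secondary events and SAEs without a sparse-event exception, at a trial size where this can fail. For an outcome at about 1 per 100 patient-years or less in both arms, the chance of an empty arm is 60% or higher; at 2 it is 25% and at 3 it is 10%. These figures assume Poisson counts, equal rates and 100 patient-years per arm. That systemic embolism, myocardial infarction or non-ICH intracranial haemorrhage are this rare is plausible but assumed.

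The loss is confined to the between-arm ratio for such outcomes: no finite estimate and no usable Wald interval. Strictly undefined is too strong a description unless both arms are empty. In that case no method gives an informative ratio, and only the per-arm rates carry information.

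**What to change.** In the Statistical analysis section, or in the announced analysis plan, replace the blanket rule for other events and SAEs with three statements:
1. For each outcome, report events, patient-years and the annual rate per arm with an exact Poisson 95% CI.
2. Where an arm has few events or none, compare arms by the exact conditional Poisson rate ratio with its 95% CI. A Firth-penalised Cox estimate or a profile-likelihood Cox interval is an acceptable alternative if a hazard ratio is wanted. Otherwise keep the Cox hazard ratio.
3. Fit no adjusted model below an event count fixed before the data are seen. Five events per arm could serve as the threshold for both rules; this number is a judgement and should be set by the trial team.

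The cost is a few sentences, with no change to data collection or trial size. The downside is that sparse outcomes are reported as rate ratios while commoner ones have hazard ratios, so tables must label the measure. The exact interval is also conservative.

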### Eligible patients

Patients with AF who recently had an ICH during the use of anticoagulation, in whom there is clinical equipoise regarding the optimal medical treatment for the prevention of stroke, are eligible for participation in this trial. The ICH should have occurred between 7 and 90 days prior to randomisation. The CHA_2_DS_2_-VASc score should be 3 or higher [8] and the score on the modified Rankin Scale (mRS) [45], as a measure for disability, 4 or lower. Detailed eligibility criteria are shown in Table 1.

**Table 1 Tab1:** Eligibility criteria

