### Study parameters

We will collect the following parameters: 1) information about the index ICH, including date, National Institutes of Health Stroke Scale score [46], location and volume of the ICH assessed on computed tomography (CT) or magnetic resonance imaging (MRI), antithrombotic medication and INR; 2) previous medical history, including cardiovascular risk factors and previous cardiovascular events, and all variables comprising the CHA_2_DS_2−_VASc [8] and HAS-BLED [47] scores; 3) blood levels of haemoglobin, liver enzymes, and creatinine, and calculated glomerular filtration rate; 4) at the time of randomisation: the score on the mRS, blood pressure, and the Informant Questionnaire on Cognitive Decline in the Elderly (IQCODE), to screen for cognitive decline prior to the index ICH [48].

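### The mRS is cut at 0-2 versus 3-6 although patients may enter at mRS 3 or 4, so worsening or death in those patients mostly does not register in the functional-outcome risk ratio

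*Protocol article*

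**What the plan says.** Four statements in the protocol article bear on this point.

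- **Entry (Eligible patients).** The condition is "the score on the modified Rankin Scale (mRS) [45], as a measure for disability, 4 or lower", so grades 0 to 4 are admissible. Entry is 7 to 90 days after the haemorrhage.
- **Outcome (Study outcomes).** One of the secondary outcomes is "functional outcome as assessed with the score on the mRS at 6 and 12 months; annually thereafter; and at the end of the study".
- **Analysis (Statistical analysis).** "We will dichotomise the mRS scores at follow-up into 3 to 6 (poor outcome) and 0 to 2 (good outcome"; then "The effect of the treatment on the mRS will be analysed using risk ratios with a corresponding 95 % CI". The same section adds: "We will adjust the crude hazard ratios and risk ratios for possible baseline incomparability given the size of the study". The covariates are not named, and a final analysis plan is to follow.
- **Baseline data (Study parameters, Randomisation).** The mRS is recorded "at the time of randomisation: the score on the mRS, blood pressure". It is not an allocation factor: allocation is stratified by intended antiplatelet use in the comparator arm and "will use a minimisation algorithm for age (≤75 years versus >75 years) and location of the haemorrhage (lobar versus non-lobar".

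The article states no ordinal analysis, no analysis of change from entry, and no distribution of mRS at entry.

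**The concern.** The cut and the entry limit do not fit together. Two of the five admissible entry grades already lie in the poor category. A patient who enters at 3 and has a disabling stroke leading to 5, or who enters at 4 and dies, is classed as poor both before and after. Only recovery to 0-2 can move such a patient.

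This matters because the two strategies trade ischaemic stroke against haemorrhage. The primary outcome counts every non-fatal stroke alike, and the mRS is the listed outcome that grades non-fatal events by their consequence. The trial is meant to inform the design of a phase III trial. A functional effect estimate pulled towards 1 by the choice of cut would be a poor guide for that purpose, even if nobody tests it.

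**Working it through.** **The plan's own figure.** The article gives no sizing or precision figure for the mRS. Its only such figure is the interval 4.9 to 17.6 for 10 primary events in 100 patient-years. The exact binomial interval for 10/100 is 4.90 to 17.62, so the figure is reproduced, but it does not bear on this point.

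**Step 1: logic, with no assumption.** Entry grades are 0, 1, 2, 3, 4, and the poor category is 3 to 6. For entry grade 3, the moves to 4, 5 or 6 stay in the poor category. For entry grade 4, the moves to 5 or 6 stay there. The binary result differs only for a patient who would otherwise have reached 0-2.

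**Step 2: how many patients.** The article does not say. The Background gives 45% dying after this type of haemorrhage and 17% recovering without disability. That leaves 100 - 45 - 17 = 38%, so 38/55 = 69% of survivors have some disability, of unstated grade. Ethical considerations expects a large proportion of survivors to be incapacitated. Both suggest that the share at mRS 3-4 is not small, but neither fixes it. A range of 30-70% is assumed.

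**Step 3: dilution.** Let s be the share entering at 3-4, w the risk of worsening or death (the same at every entry grade), and r the probability that an entrant at 3-4 who does not worsen recovers to 0-2. Then

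P(poor) = (1 - s)·w + s·[1 - (1 - w)·r].

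Assume w = 0.30 in one arm and 0.15 in the other, a true risk ratio of 0.50. With s = 0, power at 50 per arm (two-sided 5%) is 43%.

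| s | r | P(poor), w = 0.30 | P(poor), w = 0.15 | Risk ratio | Power |
|---|---|---|---|---|---|
| 0.30 | 0 | 0.510 | 0.405 | 0.79 | 18% |
| 0.50 | 0 | 0.650 | 0.575 | 0.88 | 12% |
| 0.70 | 0 | 0.790 | 0.745 | 0.94 | 8% |
| 0.30 | 0.30 | 0.447 | 0.329 | 0.73 | 23% |
| 0.50 | 0.30 | 0.545 | 0.448 | 0.82 | 16% |
| 0.70 | 0.30 | 0.643 | 0.567 | 0.88 | 12% |

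For the first row: 0.70 × 0.30 + 0.30 = 0.510; 0.70 × 0.15 + 0.30 = 0.405; 0.405/0.510 = 0.79. The formula is lenient to the plan, because it treats every worsening from 0-2 as crossing the cut. In fact the moves 0 to 1, 0 to 2 and 1 to 2 are also hidden.

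**Step 4: comparison with a full-scale analysis.** The simulation had 50 per arm, one year, and 40%, 56% or 65% entering at mRS 3-4. A first event occurs at an exponential yearly rate and moves the mRS by +1, +2, +3 or to death with probability 0.25, 0.25, 0.10 and 0.40. Patients without an event drift by -1, 0 or +1 with probability 0.20, 0.65 and 0.15. All of these are assumptions. Both tests hold about 4-6% under the null.

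| Event rates per year | Crude 0-2 v 3-6 risk ratio rejects | Rank test stratified by entry mRS rejects |
|---|---|---|
| 5% v 30% | about 10-15% | about 43-47% |
| 10% v 20% | 4-7% | 11-13% |

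Runs with slightly different splits of grades within the two entry groups reach 50% for the rank test in the first row.

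**The case against.** Several points on the other side have force.

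- **Adjustment is planned.** A reader might infer that the analysis ignores baseline mRS and that chance imbalance in it passes straight into the result. The article does not support that: it commits to adjusting the risk ratios for baseline incomparability, and naming the covariates is ordinary content for the later analysis plan. Adjustment does not, however, recover changes that the cut never records.
- **Recovery is possible.** It is tempting to say that decline in entrants at 3-4 can never affect the result. With entry as early as day 7, some would have recovered to 0-2, and an event that prevents this does count. The r = 0.30 rows show that the dilution becomes smaller but remains.
- **The hidden share has no simple value.** One might equate the share of deteriorations hidden with the share entering at 3-4. That is not correct, because moves within 0-2 are hidden too and prevented recoveries are not.
- **The large power gap needs an extreme effect.** Rates of 5% v 30% are a six-fold contrast, whereas the article's illustration is 10 events per 100 patient-years. At 4.5% v 10% the crude risk ratio rejects in 4-6% of simulated trials and the rank test in about 7%, so neither is informative at this size. Part of the gap also comes from baseline stratification: at 5% v 30% a baseline-stratified risk ratio reaches 16-30%.
- **Limited reach.** The mRS is secondary in a phase II estimation trial and is reported as a risk ratio with an interval. Deaths and strokes are analysed in their own right.
- **Independence (0-2) is a legitimate, readable outcome.** This stands, and is the reason to keep the cut as a supporting result.

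**Conclusion.** The point holds in a limited form. The cut and the entry limit are both fixed in the article, and by logic alone the mRS risk ratio does not register worsening or death in entrants at 3-4 who would not have recovered to 0-2. The planned adjustment does not cure this.

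The size depends on figures that the article does not give. With 30-70% entering at 3-4 and equal risk across grades, a true halving of worsening or death shows as a risk ratio of 0.73 to 0.94, depending on share and recovery. The gain in power from a full-scale analysis is large only for an extreme treatment contrast and small for moderate ones.

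A reader might infer that the trial would miss a difference in death or stroke. The documents do not support that, since those outcomes are analysed separately and the primary analysis does not use the mRS. This is a worthwhile, inexpensive improvement to a secondary analysis, not a flaw in the trial's main conclusion.

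**What to change.** Specify one of the following as the main mRS analysis:

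1. an ordinal analysis of the full scale with death as the worst grade, either a proportional-odds model adjusted for mRS at randomisation or a rank test stratified by it; or
2. a binary outcome relative to entry (worsening by at least one grade, or death), adjusted for mRS at randomisation.

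In either case, name mRS at randomisation as a covariate, and keep the 0-2 v 3-6 risk ratio as a supporting descriptive result.

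The cost is analysis wording only. Entry and follow-up mRS are already collected, so no visit or data item is added. The downside is small: a common odds ratio is harder to explain than a risk ratio and rests on a proportional-odds assumption.
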